##### Illness perceptions

The 9-item Brief Illness Perception Questionnaire (bIPQ) [31] will be used to assess participants’ cognitive and emotional illness perceptions. Participants are presented with statements about HIV such as ‘how much does your illness affect your life?’. Eight items measure participants’ perceptions of the timeline, consequences, controllability, emotional effects and understanding of their HIV on a scale of 0–10 with anchors relevant to each dimension, where higher scores indicate a greater strength of belief in the particular dimension. The final item asks participants to specify the 3 most important factors that they believe caused their condition. A total score will be calculated by reverse scoring 3 items and adding them to the total score of the remaining 5 items. A higher score reflects a more threatening view of the illness.

##### Self-reported adherence

Adherence to ART is measured using the Medication Adherence Report Scale-5 item version, (MARS-5) [32] consisting of 5 statements about different ways in which the participant might take their medication e.g. ‘I forget to take my medicines,’ scored on a 5-point Likert-type scale, where 1 = always and 5 = never. The statements are introduced in a non-threatening manner in order to minimise social pressure to under-report nonadherence. Adherence is expressed as a continuous scale with possible scores ranging from 5 to 25 with higher scores indicating greater adherence.

##### ART intrusiveness

The ART Intrusiveness Scale [33] consists of 10 questions which assesses the frequency and magnitude that the participants’ medication interferes with different aspects of their lives. This measure consists of 10 statements about ways in which the medication intrudes in their life, e.g. ‘My ART restricts my ability to travel’, scored for frequency on a 5-point Likert-type scale, where 1 = never and 5 = always, and magnitude of the intrusion also on a 5-point Likert-type scale, where 1 = low interference and 5 = high interference. The items are summed for both frequency and magnitude of intrusion and higher scores indicate greater intrusion.

##### Readiness to initiate ART

HIV Treatment Readiness Scale. Following a treatment offer, patients’ perceived readiness to initiate ART will be measured using a single item developed for this study “I feel ready to start antiretroviral medication”. The participant is asked to indicate the extent to which they agree or disagree with this statement on a 5-point Likert-type scale with response anchors “not ready” and “very ready.” This item was created based on the ‘readiness ruler’ [34], a motivational interviewing technique used within the SUPA intervention.

##### Knowledge about HIV treatment

Patients’ knowledge about HIV treatment will be measured using 13 items from the HIV Treatment Knowledge Scale [35]. The original scale consists of 21 items assessing knowledge about HIV and its treatment, e.g. “HIV medications help the body’s immune system get stronger (CD4 increase)”. Eight items were removed either because they assessed knowledge about transmission rather than treatment, or because the topic had been measured in other study questionnaires. Participants are required to indicate whether they believe each statement is true or false or whether they do not know the answer. A total score is calculated by summing the number of correct responses and dividing by the total number of scale items. This yields a percentage of correct responses, with higher scores indicating greater HIV treatment knowledge.

### Qualitative data

A subset of at least 20 participants receiving the SUPA intervention will be interviewed by a RA within 3 months of receiving the last intervention session. To avoid bias, the RA will be independent to the RN delivering the intervention. The interview schedule will explore participants’ perceptions of the intervention (e.g. overall impression, positive features, room for improvement, ease of comprehension, perceived effect on adherence and overall wellbeing). Transcripts will be subjected to thematic analysis.

### Sample size calculations

#### Phase 1 - observational cohort

Our risk assessment for nonadherence was based on the findings of a previous prospective study of beliefs and adherence among PLWH [19]. Phase 1 assesses whether the initial risk assessment is valid in the current sample. As such we will not aim to obtain a particular sample size, but rather recruit as many patients as possible (all eligible patients attending the clinic will be invited to Phase 1).

#### Phase 2 – trial

Since this study uses a novel measure combining both uptake and adherence, there are no data to inform a sample size calculation. It is plausible that the distribution could be bimodal or highly skewed. As the proportion with ≥90% adherence will also be bounded by [0,1], standard sample size calculations based on the normal distribution would likely be inappropriate, even if a standard deviation could be hypothesised. This study therefore defines a good primary outcome as ≥80% of follow-up months with ≥90% adherence. Since the study selects for an at-risk group, we would expect a large difference between control and intervention groups, and a 15% difference between groups is considered clinically significant based on estimated intervention costs. Table 1 shows the number of participants needed in each arm to detect a 15% difference in adherence from a range of possible control group percentages with > = 0.8 of follow-up months with ≥90% adherence (80% power, 2-sided alpha = 0.05). We will therefore recruit 372 participants.

**Table 1 Tab1:** Sample size calculations for Phase 2 – trial

Standard of care group % with > 0.8 of follow-up months with ≥90% adherence	Intervention group % with > 0.8 of follow-up months with ≥90% adherence	N per arm	Total N
35%	50%	183	366
45%	60%	186	372
50%	65%	183	366
60%	75%	165	330
70%	85%	134	268

### Statistical methods and analysis

The SUPA intervention is hypothesised to be superior to care as usual, and therefore the planned analysis is intention to treat, including all randomised participants, with all participants analysed according to the study group to which they were randomised regardless of subsequent treatment received. Primary analysis will include all randomised participants other than those randomised in error (defined as not intending to randomise the participant through e.g. miscommunication, rather than a participant or clinician decision once the allocation has been given).

A per-protocol analysis will be carried out on the primary endpoint including all participants in the intervention group who attended all 4 (2 + 1 + 1) sessions. If the intention to treat and per-protocol analyses on the primary endpoint leads to inconsistent results, then per-protocol analysis will also be carried out on all the other endpoints.

Continuous variables will be summarised by medians and IQRs or means and standard deviations as appropriate depending on the distribution, and compared between groups using ranksum tests or t-tests respectively. Comparisons of change from baseline in continuous variables will adjust for any baseline imbalances using either quantile or normal linear regression (depending on the shape of the distribution).

Categorical variables will be summarised by frequency tables, and compared between groups using chi-squared tests, unless any cell count is < 5 or cell percentage is < 5% in which case exact tests will be used. Binary variables will be summarised by percentages, using standard exact 95% CI for the risk differences. Time-to-event variables will be summarised using Kaplan-Meier curves and average differences between randomised groups estimated using Cox models. Patients without the event recorded will be censored at their last clinic visit. Proportionality of hazards will be tested; where significant departures exist, varying differences between randomised groups over time will be estimated using flexible parametric models of Royston and Parmar. Rate of treatment switching will be analysed using Poisson regression, including all changes to ART as events and the total time under follow-up through the earliest of 12 months or the last patient visit as the person-time at risk. Primary analysis will not stratify by clinical centre.

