### Randomisation

If the participant consents to participate in Phase 2, they will be randomly allocated to one of the two trial arms (open randomisation; ratio 1:1) by the King’s Clinical Trials Unit (KCTU), King’s College London. The randomisation procedure will be a stratified block randomisation. Centres will be blocked to ensure that there are equal participants in each arm at each site. The randomisation schedule will be incorporated into a dedicated electronic database and kept securely within this electronic system, inaccessible to the enrolment location. Once an eligible participant has given written informed consent and completed the baseline assessment, the RA will log on to the randomisation system, enter the participant identification number and hospital, and will click on the ‘randomise’ function. The treatment allocation will appear immediately on screen and be communicated to the patient. The confirmation of treatment allocation details will be sent to the research team immediately. The RA will inform the participant’s HIV clinical team on the same day. Movement from the observational cohort to the intervention trial or declining participation in the trial will be recorded on the central database.

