#### Phase 2 – randomised controlled trial

For trial participants, the baseline visit includes enrolment, randomisation and completion of the trial study questionnaires (Additional file 2). For intervention participants, this includes their first intervention session. Participants in the intervention arm will then be invited to attend additional study visits at 1, 3, 6 and 12-months post-randomisation. Participants in the control arm will be invited to attend additional study visits at 3, 6 and 12 months post-randomisation (Fig. 1). Expenses for study visits will bereimbursed (£10 per visit).

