#### Patient-reported endpoints

##### Changes in perceptions of ART between baseline and 12 months

Perceptions of ART will be measured using the BMQ-ART [16, 18] which was adapted following preparatory work with the target populations [23] to include items on culturally-specific and practical barriers specific to ART. The BMQ-ART includes 2 scales: the ART-Necessity scale and the ART-Concerns scale. The ART-Necessity scale consists of 10 items which assess how patients perceive their personal need for ART for keeping their HIV under control, maintaining their health and preventing illness. The ART-Concerns scale consists of 10 items measuring concerns about potential adverse effects of ART that have been identified in previous studies. These include fears about short- and long-term side effects, concerns about the timing of tablets and the disruptive effects of the ART regimen on daily life. Participants are asked to rate the extent to which they agree with each item on a scale with possible responses ranging from strongly agree (scored 5) to strongly disagree (scored 1). A total score for each scale is computed by adding the scores for each scale item together and dividing by the number of items. This yields a mean score ranging from 1 to 5 for the necessity and concerns scales.

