##### Depression and anxiety at 12 months

The Hospital Anxiety and Depression Scale (HADS) [24] will be used to measure anxiety and depression. This 14-item measure was designed to detect the presence and severity of anxiety and depression among patients attending outpatient clinics without the possibility that scores would be contaminated by reporting of physical symptoms. Possible responses for each item ranged from 0 to 3, with each seven-item scale having a total possible score range of 0 to 21. Higher scores indicate greater anxiety or depression. Good psychometric properties of the HADS have been found in studies including medical outpatients [24, 25].

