##### Health-related quality of life at 12 months

The Euroqol-5D (EQ-5D-5 L) is a self-completed measure of health-related quality of life (HRQoL), comprising 5 questions relating to dimensions of health: mobility, self-care, ability to undertake usual activities, pain/discomfort, and anxiety/depression [26]. Each dimension has 5 levels from ‘no problems’ (scored 1) to ‘extreme problems’ (scored 5). This results in a score on each dimension that can be combined to a 5-digit number describing the patient’s state of health. These health states will be combined with population weights to estimate individual utility scores ranging from 0 (worst health) to 1 (full health), required for generating quality-adjusted life years [27, 28]. The scale also includes a visual analogue scale (EQ-VAS) where the participant is required to indicate their level of health on a vertical scale with endpoints labelled ‘the best health you can imagine’ and ‘the worst health you can imagine’. This score (from 0 to 100) represents the patient’s judgement of their own health.

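### Continuous secondary outcomes should always be adjusted for their own baseline value; as worded, some are tested unadjusted and the adjustment of others is unclear

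*Protocol article*

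**What the plan says.** The protocol article gives two rules for continuous variables under Statistical methods and analysis.

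- The general rule: they are summarised by means or medians according to their distribution and "compared between groups using ranksum tests or t-tests respectively". No covariate is named.
- The rule for change scores: "Comparisons of change from baseline in continuous variables will adjust for any baseline imbalances using either quantile or normal linear regression", the choice depending on the shape of the distribution.

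The secondary endpoints are worded in two ways. BMQ-ART is a change: "Changes in perceptions of ART between baseline and 12 months". HADS and EQ-5D are levels: "Depression and anxiety at 12 months" and "Health-related quality of life at 12 months".

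Baseline scores exist, since for trial participants "the baseline visit includes enrolment, randomisation and completion of the trial study questionnaires". BMQ-ART is also scored at entry, because it decides who is invited to the trial (Recruitment). The article nowhere makes an outcome's own baseline value a fixed covariate.

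**The concern.** In a randomised trial any baseline difference between arms is due to chance. The reason to adjust for a baseline score is that it predicts the later score and so removes noise from the comparison. That reason applies whether or not the arms happen to differ at baseline.

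Two consequences follow from the wording:

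- Outcomes defined as a 12-month level are compared without using a baseline score that the trial collects.
- For change outcomes, adjustment is tied to imbalances. No variable list and no criterion is given. If adjustment depends on what is observed, the model is settled only after the data are seen, and precision is lost whenever no imbalance is declared.

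BMQ-ART matters most here. Beliefs about ART are the route by which the intervention is meant to work, and the article says it will examine that mechanism. The sample size is set for the binary primary endpoint alone, so precision on these scales is whatever the analysis can extract.

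**Working it through.** **The plan's own figure.** The only sample size figure is for the binary primary endpoint (Sample size calculations, Table 1): 45% against 60%, "80% power, 2-sided alpha = 0.05", "open randomisation; ratio 1:1", giving 186 per arm.

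- Pooled formula: n₀ = [1.960·√(2·0.525·0.475) + 0.842·√(0.45·0.55 + 0.60·0.40)]² / 0.15² = 172.8, that is 173.
- With continuity correction: n = (n₀/4)·[1 + √(1 + 4/(n₀·0.15))]² = 185.9, that is 186.

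All five rows of Table 1 reproduce this way (183, 186, 183, 165, 134). The point below does not touch them. The article gives no power or precision figure for the continuous secondary endpoints.

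**Inputs for those endpoints.** 186 per arm is from Table 1, taken with no loss to follow-up. The baseline-to-12-month correlation r is not in the document, so 0.3 to 0.7 is assumed. Equal SDs at both times and a linear model are also assumed.

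**Formulas.** The variance of the difference between arms is (2·SD²/n) times:

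- 1 for an unadjusted 12-month comparison;
- 1 − r² for the 12-month value adjusted for baseline;
- 2(1 − r) for a raw, never-adjusted change score.

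The detectable difference at 80% power is (1.960 + 0.842)·√(2·factor/186), in SD units.

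**Unadjusted 12-month test against baseline adjustment**

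| r | 1 − r² | Variance ratio, unadjusted to adjusted | Detectable, unadjusted | Detectable, adjusted | Adjusted n per arm matching 186 unadjusted |
|---|---|---|---|---|---|
| 0.3 | 0.91 | 1.10 | 0.291 SD | 0.277 SD | 169 |
| 0.5 | 0.75 | 1.33 | 0.291 SD | 0.252 SD | 140 |
| 0.7 | 0.51 | 1.96 | 0.291 SD | 0.207 SD | 95 |

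The variance ratios do not depend on n, so loss to follow-up shared by both analyses leaves them unchanged. For a true difference of 0.29 SD, power is 80% unadjusted and 83%, 90% and 97.5% adjusted.

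**Change scores, if adjustment depends on imbalance.** A raw change score has 2(1 − r)/(1 − r²) = 1.54, 1.33 and 1.18 times the adjusted variance. A simulation (20,000 runs, 186 per arm, no true effect) used raw change unless baseline differed at p < 0.05, and baseline adjustment otherwise. That threshold is assumed, since the article gives none.

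| r | SE, conditional rule | SE, always adjusted | Type I error, conditional rule |
|---|---|---|---|
| 0.3 | 0.117 SD | 0.100 SD | 4.1% |
| 0.5 | 0.099 SD | 0.089 SD | 4.1% |
| 0.7 | 0.079 SD | 0.074 SD | 4.6% |

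The conditional rule does not inflate the error rate; it loses precision.

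**Change scores, if baseline is always in the model.** If Y − X = a + b·arm + c·X, then Y = a + b·arm + (c + 1)·X. The arm effect b and its standard error are the same as when the 12-month value is regressed on arm and baseline. The same identity holds for quantile regression. On this reading nothing is lost for change outcomes.

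**The case against.** The strongest reply is that the change-score sentence contains no condition. It names no test and no threshold, and it can be read as always fitting a regression that removes whatever baseline difference there is. By the identity above, BMQ-ART would then already have the recommended analysis. This stands as a possible reading. A reader might infer that the model will certainly be chosen after inspecting imbalance, or that the raw-change ratios of 1.54, 1.33 and 1.18 describe the plan. The text supports neither; both hold only under the conditional reading.

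It can also be said that the article never assigns HADS or EQ-5D to the unadjusted tests by name, and that the analysis plan may do otherwise. The assignment does rest on the endpoint headings. But the article states a rule for continuous variables, and that rule carries no covariate.

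Other stronger inferences also fail:

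- **Validity.** The unadjusted tests are valid under randomisation.
- **Regression to the mean.** Entry requires Necessity ≤ 3 and/or Concerns ≥ 3, so scores may drift back towards average. Both arms are selected alike, so this cancels in the randomised comparison. Selection also restricts the baseline range and may lower r for BMQ-ART, towards the 10% end for the unadjusted comparison.
- **QALYs.** Costs and QALYs have their own methods under Health economic analyses. Nothing there shows that QALY intervals would be too wide.
- **Size.** The ratios are for linear models and do not carry over directly to rank-sum tests or quantile regression.

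**Conclusion.** The point holds as one of precision and clear wording on secondary endpoints. As written, outcomes headed as 12-month levels fall under unadjusted tests, and whether BMQ-ART change is always adjusted for baseline is left open. The primary endpoint and the 372 are unaffected.

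The unadjusted 12-month comparison has 10%, 33% or 96% more variance than the adjusted one at r = 0.3, 0.5 or 0.7. The direction is certain for any r above 0; the size depends on an r that the document does not give, and on equal SDs and a linear model. It is further assumed that HADS and EQ-5D are among the baseline questionnaires, whose list is in an additional file not shown. A data-dependent model is an added cost only under the conditional reading of the change-score sentence.

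**What to change.** Replace both rules, for outcomes with a baseline measure, by one: regress the 12-month value on randomised arm and the outcome's own baseline value, whatever the observed imbalance. Use the linear or quantile regression that the plan already names, and report the adjusted difference with its 95% CI.

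Name the scales covered: BMQ-ART Necessity and Concerns, HADS anxiety and depression, EQ-5D and EQ-VAS and, if measured at baseline, the illness perception and treatment knowledge scores. Leave out MARS-5 and ART intrusiveness, which presuppose taking ART and so have no meaningful baseline in participants entering ART-naive.

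This needs no centre covariate, and quantile regression need not be demoted to a sensitivity analysis. The cost is a sentence or two of wording, with no new data and no change to the sample size. The article reports that no data cleaning or analysis had been done when it was submitted, so at that stage the rule could still be fixed in advance.

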## Methods

### Study design

This study comprises 2 phases (Fig. 1). Phase 1 is an observational cohort study, in which PLWH who are ART naïve and recommended to take ART by their clinician complete a questionnaire assessing their beliefs about ART over a period of 12 months. Phase 2 is a randomised controlled trial (RCT) nested within the observational cohort study to investigate the effectiveness of the SUPA intervention on adherence to ART and to explore the intervention mechanism. PLWH who are at risk of nonadherence will be recruited and randomised 1:1 to the intervention and control arms. All participants will receive usual care which is provided to all NHS patients through clinical support from a multi-disciplinary healthcare team including the patient’s assigned HIV physician, nurses, pharmacists and other healthcare professionals, such as clinical psychologists, as required. In addition, participants in the intervention arm will receive the SUPA intervention.

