### Recruitment

A two-stage enrolment process will be employed: Patients who meet the inclusion criteria will be informed about the study by their HIV doctor, and will subsequently be referred to the study team. All patients who meet the inclusion criteria will be invited to participate in the observational component of the study (Phase 1). Following informed consent, all participants will complete the Beliefs about Medicines Questionnaire-ART specific version (BMQ-ART). The clinician or Research Assistant (RA) will score the questionnaire immediately. If the score indicates that the participant is at high risk for nonadherence (ART-Necessity score ≤ 3 and/or ART-Concerns score ≥ 3), they will be provided with information by the study team and invited to consider taking part in Phase 2, the interventional trial component. Further written informed consent to take part in Phase 2 will be received after the patient has been given an opportunity to consider their participation in the study and discuss this with others if they wish.

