### Subgroup analyses

Subgroup analyses will be performed to assess heterogeneity in differences between randomised groups for the primary endpoint according to gender, ethnicity, number of intervention sessions attended, early (treatment indicated at point of diagnosis) vs late diagnosis (treatment not indicated at point of diagnosis), starting for clinical need vs starting for treatment as prevention, baseline CD4 count, and baseline BMQ scores - low Necessity vs high Concerns vs both low Necessity and high Concerns. Subgroup analyses will use logistic regression to model interactions between randomised group and the factors above.

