## Discussion

We have described the design of the Supporting Uptake and Adherence to ART (SUPA) trial, an observational cohort study with nested randomised controlled trial evaluating the effectiveness of a CBT-based intervention to increase uptake and adherence to ART by addressing perceptual and practical barriers.

The intervention is based on the Necessity Concerns Framework and aims to address both perceptual and practical barriers to adherence as recommended by NICE [20] and BHIVA guidelines [9]. The intervention has been developed according to published guidelines for the development of complex interventions [15] and builds on preparatory research with PLWH showing that uptake and adherence to ART is driven by patients’ perceptions of their personal necessity for ART and concerns about adverse effects [18, 19]. To our knowledge, this is the first study to provide support at the time of a treatment recommendation to PLWH who may be at risk of delaying uptake or developing issues with adherence. This study targets individuals who may be considered as being hard to reach, and who are not usually represented in randomised trials. The study design allows the examination of process variables and the mechanism by which the intervention exerts its effect. The cost effectiveness analysis will enable health-care service providers to make informed decisions about the value of the intervention.

While it was not possible to mask the allocation of participants to intervention or control groups, we have taken steps to reduce bias, including blinding of the statistical team to group allocation and ensuring that data is not collected or entered by those delivering the intervention. It possible that the primary outcome measure (MEMS) may impact on adherence as it serves as a reminder to participants that they are monitored. However, the impact of adherence monitoring alone is likely to be minimal [36]. Although participants are selected for risk of delay to initiate treatment and nonadherence using a screening tool (BMQ-ART), patients who decline to take part in the study may represent a different group who are more at risk of disengaging from care. However, these participants will be followed up in the observational cohort, therefore their virological outcomes can be compared with those of trial participants.

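### The only analysis stated for the binary primary endpoint is unadjusted, although the protocol records before randomisation the belief scores it says drive the outcome: a low-cost efficiency gain, not an error

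*Protocol article*

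**What the plan says.** The Primary endpoint section splits participants by whether at least 0.8 of their follow-up months reached 90% adherence, so the outcome is binary. Statistical methods and analysis sets methods by type of variable. Categorical variables get chi-squared tests, or exact tests when cells are small. For binary outcomes: "Binary variables will be summarised by percentages, using standard exact 95% CI for the risk differences". Baseline adjustment is mentioned only for change from baseline in continuous variables. The section also rules out stratifying the primary analysis by centre, which is a separate matter from this point.

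On the covariates, Recruitment says that after consent "all participants will complete the Beliefs about Medicines Questionnaire-ART specific version (BMQ-ART", and the questionnaire is scored at once to decide who may enter the trial. The Randomisation section places the baseline assessment before allocation. The Discussion says preparatory work showed that "uptake and adherence to ART is driven by patients’ perceptions of their personal necessity for ART and concerns about adverse effects". In the modelling of the primary endpoint, baseline BMQ-ART appears only as a subgroup factor: "Subgroup analyses will use logistic regression to model interactions between randomised group and the factors above".

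The sample size rests on "80% power, 2-sided alpha = 0.05" and a 15-point target, since "a 15% difference between groups is considered clinically significant based on estimated intervention costs". The largest row of Table 1 is 45% vs 60%, with 186 per arm, and "We will therefore recruit 372 participants".

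**The concern.** Participants are ART-naive, apart from some women with earlier ART in pregnancy, so there is no useful baseline value of the outcome to adjust for. The belief scores are the nearest substitute: they are the trial's own risk marker and are measured before allocation in everyone randomised. If they still predict adherence among those randomised, leaving them out of the primary comparison leaves explainable variation in its error. Randomisation is described as blocked by centre only, so neither design nor analysis controls chance imbalance on these scores, whereas change outcomes are to be adjusted for baseline imbalance. What is at stake is the precision of the main result, not its validity.

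**Working it through.** **Inputs from the article.** Two-sided alpha 0.05, power 80%, control 45%, intervention 60%, 1:1 allocation, 186 per arm, 372 in total (Sample size calculations, Phase 2 – trial; Study design). **Not in the article:** the correlation rho between the baseline scores and the binary outcome within the at-risk group. It is assumed below.

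**1. Reproduce Table 1.** The pooled formula with mean proportion 0.525 gives

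m = [1.96·√(2·0.525·0.475) + 0.8416·√(0.45·0.55 + 0.60·0.40)]² / 0.15² = (1.384 + 0.588)² / 0.0225 = 172.8.

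The continuity correction gives (m/4)·[1 + √(1 + 4/(0.15·m))]² = 43.2 × (1 + 1.0744)² = 185.9, so 186 per arm. The same formula returns 183, 186, 183, 165 and 134, matching all five rows. Without the correction the rows would be 170, 173, 170, 152 and 121.

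**2. Power of the stated analysis at 186 per arm.**

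- Normal approximation: Φ[(0.15·√186 − 1.384)/0.698] = Φ(0.947) = 82.8%.
- Exact enumeration of the two binomials, pooled z test: 83.8%.
- Same enumeration with continuity correction: 81.1%; Fisher's exact test also gives 81.1%.

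All exceed the stated 80%.

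**3. What adjustment could add.** As a first approximation, adjusting for a covariate with correlation rho acts like a sample of 372/(1 − rho²): 372/0.96 = 388 at rho 0.2 and 372/0.91 = 409 at rho 0.3. The table gives simulated power at 45% vs 60%, 186 per arm, with one standard normal score and the marginal rates held fixed. It compares the pooled z test with the Wald test for arm in the adjusted logistic model.

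| Assumed rho | Unadjusted | Adjusted | Gain (points) | Runs |
|---|---|---|---|---|
| 0 | 82.4% | 81.5% | −0.9 | 4000 |
| 0.11 | 84.2% | 83.4% | −0.8 | 6000 |
| 0.19 | 84.5% | 84.7% | +0.2 | 6000 |
| 0.26 | 84.2% | 85.4% | +1.2 | 6000 |
| 0.29 | 85.0% | 86.4% | +1.4 | 4000 |
| 0.31 | 84.2% | 86.6% | +2.4 | 6000 |
| 0.36 | 84.8% | 88.4% | +3.6 | 4000 |
| 0.38 | 83.8% | 88.6% | +4.8 | 6000 |

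The unadjusted column should be constant at about 83.8%. Its scatter is simulation error, with a standard error of about √(0.84·0.16/4000) = 0.6 points at 4000 runs and 0.5 at 6000, so the gains are good to about a point. For the standardised risk difference, precision matched about 408 unadjusted patients at rho 0.31 and about 432 at rho 0.38. The formula gives 372/(1 − 0.31²) = 412 and 372/(1 − 0.38²) = 435.

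**4. Which rho is plausible.** Entry requires Necessity at or below 3, Concerns at or above 3, or both. For assumed screening means of 3.5 to 3.9 (Necessity) and 2.7 to 3.0 (Concerns), SD 0.6 and correlation −0.3, the variance of Necessity minus Concerns among those selected is 0.50 to 0.55 of that among all screened. Concerns alone falls to 0.43 to 0.57. Necessity alone hardly changes (0.97 to 1.06). If the variance halves, the usual range-restriction formula takes a rho of 0.4 among all screened to √[0.16·0.5/(0.84 + 0.16·0.5)] = √(0.08/0.92) = 0.29 in the trial.

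**5. Chance imbalance.** One standard error of the between-arm difference in a score is √(2/186) = 0.10 SD. At rho 0.31 the outcome moves about 0.31 × 0.50 = 15.5 points per SD, so an imbalance of one standard error shifts the unadjusted estimate by about 1.6 points and two by about 3.2, against a 15-point target.

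**The case against.** The strongest reply has four parts.

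- **Nothing stated is wrong.** A chi-squared test with an exact interval for the risk difference is valid, targets the 15-point difference used for sample size, and meets 80% power. This stands.
- **Covariate choice is normally left to the statistical analysis plan, which is not shown.** No sentence in the article names the test for the primary endpoint. This stands in part. The unseen plan may already adjust, in which case only the article's wording is out of step. But the article does state a method for binary outcomes, it is the only one given, and it is unadjusted.
- **Prognostic strength in this sample is an open question.** The Phase 1 sample size section says that phase will test whether the risk assessment holds here. Entry is also selected on the scores. Both facts stand, and they are why the size can only be conditional.
- **Chance imbalance does not bias the unadjusted estimate over repeated randomisation, and its interval already allows for it.** This stands. The shifts shown are part of the ordinary sampling error that adjustment would reduce.

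A reader might infer more than the documents support:

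- That the trial is underpowered: Table 1 reproduces and the stated power is met.
- That a large gain is being lost: that needs a correlation of 0.4 or more after selection, for which the article gives no evidence.
- That baseline CD4 count belongs in the model: no section says it predicts adherence.
- That the belief scores serve only subgroup analyses: change in perceptions of ART is a secondary endpoint, and how beliefs predict adherence is part of a secondary objective.

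**Conclusion.** The point holds as an efficiency improvement. The stated primary comparison leaves out pre-randomisation scores that the protocol itself presents as drivers of the outcome, when using them would cost almost nothing. The gain in power is nil up to a correlation of about 0.2, about 1 to 2 points near 0.3, and about 4 to 5 points at 0.35 to 0.38. These figures assume 45% vs 60%, 186 per arm and a single normally distributed score related to the outcome through a logistic model. The correlation is an assumption throughout, and selection on the same scores favours the lower part of the range. The analysis as written remains valid and adequately powered.

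**What to change.** Before any analysis, prespecify the primary analysis as a logistic regression of the responder outcome on randomised arm with baseline ART-Necessity and ART-Concerns scores, both continuous. Report the standardised (marginal) risk difference with a 95% CI, so that the quantity estimated is still the 15-point difference behind the sample size. Retain the unadjusted test and exact CI as a sensitivity analysis. Baseline CD4 count may be added but is optional. If the statistical analysis plan already adjusts for the scores, align the article's text with it.

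The cost is wording. The scores are already collected, and logistic models of this endpoint with baseline BMQ are already planned for subgroups. Trial status reports that recruitment had closed but no cleaning or analysis had begun at submission, so the change could then still be made without knowledge of outcomes. The downsides are a model-based rather than exact interval, a power loss of under 1 point if the scores prove unrelated to the outcome, and the need for a rule on any missing baseline scores.
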